## Abstract

**Background:**

Congestive heart failure (CHF) has a substantial impact on care utilisation and quality of life. It is crucial for patients to cope with CHF adequately, if they are to live an acceptable life. Self-management may play an important role in this regard. Previous studies have shown the effectiveness of the 'Chronic Disease Self-Management Program' (CDSMP), a group-based cognitive behavioural programme for patients with various chronic conditions. However, the programme's effectiveness has not yet been studied specifically among CHF patients. This paper presents the design of a randomised controlled trial to evaluate the effects of the CDSMP on psychosocial attributes, health behaviour, quality of life, and health care utilisation of CHF patients.

**Methods/Design:**

The programme is being evaluated in a two-group randomised controlled trial. Patients were eligible if they had been diagnosed with CHF and experienced slight to marked limitation of physical activity. They were selected from the Heart Failure and/or Cardiology Outpatient Clinics of six hospitals. Eligible patients underwent a baseline assessment and were subsequently allocated to the intervention or control group. Patients allocated to the intervention group were invited to attend the self-management programme consisting of six weekly sessions, led by a CHF nurse specialist and a CHF patient. Those allocated to the control group received care as usual. Follow-up measurements are being carried out immediately after the intervention period, and six and twelve months after the start of the intervention.

An effect evaluation and a process evaluation are being conducted. The primary outcomes of the effect evaluation are self-efficacy expectancies, perceived control, and cognitive symptom management. The secondary outcome measures are smoking and drinking behaviour, Body Mass Index (BMI), physical activity level, self-care behaviour, health-related quality of life, perceived autonomy, symptoms of anxiety and depression, and health care utilisation. The programme's feasibility is assessed by measuring compliance with the protocol, patients' attendance and adherence, and the opinions about the programme.

**Discussion:**

A total number of 318 patients were included in the trial. At present, follow-up data are being collected. The results of the trial become clear after completion of the data collection in January 2007.

**Trial Registration:**

Trialregister () ISRCTN88363287.

## Background

Effective management of congestive heart failure (CHF) is one of the major challenges in health care today. The number of CHF patients is substantial: CHF affects up to 20% of the rapidly increasing population of persons aged 65 years and over. Of every three individuals aged 55 years and over, one will develop CHF during their lifetime, with only 35% surviving 5 years following diagnosis [1]. In the aging population of the Western world, this implies a further expansion of the CHF epidemic in the near future [2,3]. CHF has a substantial impact on care utilisation, daily functioning, and quality of life [4,5].

There is increasing evidence that self-management programmes for CHF patients have positive effects on self-care behaviour and quality of life [6-9]. Managing CHF is a complex task, and comparable to diabetes in that it touches nearly every important aspect of daily life [10]. It is therefore crucial for patients to cope with CHF adequately, if they are to live an acceptable life. Exercise intolerance, often experienced by CHF patients, may lead to activity restriction and progressive functional deterioration. This downward spiral may be interrupted by physical activity, which may improve functional capacity and quality of life [11]. In addition, diet and lifestyle changes, such as limiting salt intake and balancing rest and activity, are important to prevent complications and hospitalisation, and to slow the disease progression [12,13]. Self-management skills such as fatigue management, breathing techniques, and relaxation can play an important role in everyday CHF management [14].

To teach patients how to adequately self-manage the consequences of their chronic disease for daily life, Lorig and colleagues developed the "Chronic Disease Self-Management Program" (CDSMP) at Stanford University in California (USA) [14-18]. The CDSMP is a structured group-based self-management programme for people with chronic conditions, addressing general management problems for various chronic conditions. The CDSMP is based on the self-efficacy theory developed by Bandura [19] and incorporates skills mastery, reinterpretation of symptoms, modelling, and social persuasion to enhance self-efficacy expectancies [16,18]. Self-efficacy expectancies refer to the belief that one can successfully perform intended behaviours [19], and are powerful determinants of behavioural change [20]. There are indications that low levels of self-efficacy expectancies predict functional decline in CHF patients [21]. Improving self-efficacy expectancies may therefore change health behaviour, improve health-related quality of life, and reduce care utilisation by CHF patients.

Previous studies have found favourable effects of the CDSMP (e.g. on self-efficacy expectancies and hospitalisation) in arthritis patients [22] and in groups of patients with various chronic conditions attending the same class [17,23], even after one and two years [15,16]. However, the effects of the programme have not yet been studied specifically among CHF patients. Our basic assumption is that increasing levels of self-efficacy expectancies will help CHF patients to interrupt the downward spiral of functional disability and demoralisation after their cardiac event. Therefore, we decided to evaluate the effects of the CDSMP on psychosocial attributes (e.g. self-efficacy expectancies), health behaviour, quality of life, and health care utilisation of CHF patients. The current paper presents the design of a multi-centre randomised controlled trial evaluating the CDSMP among CHF outpatients in the south of the Netherlands. The study involves an effect evaluation and an evaluation of the intervention process. The process analysis is expected to yield information on factors increasing or hampering the effectiveness and implementation of the programme in outpatient care for CHF patients, which may be crucial later on if the group programme turns out to be effective.

### Aims

The main objectives of the current study are: (1) to assess the effects of the cognitive behavioural CDSMP intervention on psychosocial attributes, health behaviour, quality of life, and health care utilisation of CHF patients, and (2) to assess the feasibility of the CDSMP intervention according to patients and leaders of the programme.

## Methods/Design

### Design

This evaluation study is designed as a two-group randomised controlled trial in which patients are randomly allocated to the intervention or control group (the latter receiving usual care). Data are collected at baseline before the start of the intervention, immediately after the programme (six weeks after the start), and six and twelve months after the start of the programme (see figure 1). Data are gathered by means of self-administered questionnaires and telephone interviews. Various measures are taken to ensure blinding in the data collection process. Questionnaires are collected anonymously and sorted by number. The telephone interviews are conducted independently by trained interviewers, who are unaware to which group patients have been allocated.

For practical reasons, the study consists of eleven consecutive cycles, with one or more CDSMP classes in each cycle. In each cycle, patients are included and randomly allocated to the intervention group or control group. The first cycle started in July 2004 and the final one in September 2005. A total of 21 CDSMP classes (with a parallel control group) were conducted in the period October 2004 – January 2006, in six hospitals. At least two CDSMP classes were conducted in each participating hospital (range 2–6). The Medical Ethics Committee of Maastricht University/University Hospital Maastricht granted approval to conduct this trial. Furthermore, local feasibility of the study design was assessed by each of the local Medical Ethics Committees in the other five participating hospitals.

### Participants

Patients were selected by cardiologists or CHF nurse specialists of the Heart Failure and/or Cardiology Outpatient Clinics in the six participating hospitals. Patients were eligible for the study if they met the following four criteria: (1) having been diagnosed with CHF based on a systolic dysfunction (left ventricular ejection fraction (LVEF) < 40% with New York Heart Association (NYHA) Class II-III symptoms; slight to marked limitation of physical activity) or a diastolic dysfunction (LVEF ≥ 40% with NYHA Class II-III symptoms plus an additional hospital admission based on decompensatio cordis after CHF diagnosis); (2) having been a CHF patient for at least six months at the start of the intervention period, (3) being able to understand, write, and speak Dutch, and (4) being willing to give informed consent to participate in the study. Patients were excluded if they were participating in other scientific research. All eligible patients received written information about the programme and the study. Patients who signed the informed consent form were invited to participate in the baseline measurement.

### Randomisation

In each cycle, patients were randomised after completion of the baseline measurement if a sufficiently large group of eligible patients per hospital could be formed. We decided that at least eight patients per group had to be allocated to the intervention group, because CDSMP classes normally consist of at least eight participants, for reasons of group dynamics [16]. Eligible patients therefore had a slightly higher chance to be allocated to the intervention group (59%) than to the control group (41%) during the total recruitment period. The maximum number of patients allocated to each CDSMP class was set at 14. The randomisation procedure was performed by an independent researcher by random computerised allocation using SPSS 12.0 for Windows.

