#### Covariates

Some additional variables were assessed to characterise the study population and interpret the outcomes of the trial (see table 2). Socio-demographics (gender, age, marital status, living arrangements, education level, and job situation) were assessed at baseline. In addition, two health-related variables were assessed at baseline: co-morbidity using a 19-item checklist of medical conditions [21,38] and cognitive status using the Dutch version of the Telephone Interview for Cognitive Status (TICS) [39,40].

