### Analysis

Descriptive techniques will be used to characterise the patients participating in the study. Data of the effect evaluation will be analysed according to the intention-to-treat and per-protocol principles. Differences between the intervention and control groups with regard to the primary and secondary outcome variables at the follow-up assessments will be analysed with multivariate techniques adjusting for possible differences in baseline scores and background characteristics. Intervention group patients will be included in the per-protocol analysis if they have attended at least four of the six programme sessions.

Data of the process evaluation will be analysed for patients and leaders by means of descriptive analysis.

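### The effect analyses should include the hospital-by-cycle randomisation pool, because the share allocated to intervention probably varied between pools

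*Protocol article*

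**What the plan says.** All places are in the protocol article.

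- **Design:** "the study consists of eleven consecutive cycles, with one or more CDSMP classes in each cycle". On allocation: "In each cycle, patients are included and randomly allocated to the intervention group or control group". On delivery: "A total of 21 CDSMP classes (with a parallel control group) were conducted", in six hospitals with two to six classes each.
- **Randomisation:** the timing and unit are given as: "In each cycle, patients were randomised after completion of the baseline measurement if a sufficiently large group of eligible patients per hospital could be formed". The floor on the intervention arm is: "We decided that at least eight patients per group had to be allocated to the intervention group". A class could hold at most 14. As a consequence of the floor, the article says that patients had a "slightly higher chance to be allocated to the intervention group (59%) than to the control group (41%) during the total recruitment period".
- **Power calculation and Progress of the study:** the plan was 2 × 180. In the event 187 were allocated to intervention and 131 to control, and the article says that the control arm fell short of plan.
- **Analysis:** group differences "will be analysed with multivariate techniques adjusting for possible differences in baseline scores and background characteristics".
- **Covariates:** "Socio-demographics (gender, age, marital status, living arrangements, education level, and job situation) were assessed at baseline", together with co-morbidity and cognitive status. Hospital and cycle are named neither here nor under Analysis.

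**The concern.** The unit within which chance decided treatment is the group of patients from one hospital in one cycle. If the share going to intervention differs between these pools, the arms are comparable by design only within a pool. Pools with a high share then weigh more in the intervention arm than in the control arm. A comparison across pools therefore mixes the treatment effect with any difference in outcome course between high-share and low-share pools.

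Such differences are conceivable here. The sites are heart failure and/or cardiology clinics, so usual care may differ. Cycles started between July 2004 and September 2005, so season differs. One secondary outcome counts walking, swimming and cycling in the preceding month. Adjusting for the baseline score removes differences present at baseline but not those that develop afterwards. At stake is a shift in the estimated effect, in either direction, that more patients would not reduce.

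**Working it through.** **1. The stated split.** 187/318 = 58.8% and 131/318 = 41.2%. The printed 59:41 is therefore the realised average over recruitment. With 2 × 180 planned, it does not look like a preset ratio.

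**2. What the floor does.** Take a pool of p patients for one class, split 1:1 unless the floor binds. The intervention number is max(8, p/2), and the cap of 14 binds only above 28.

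| Pool size p | Intervention : control | Share to intervention |
|---|---|---|
| 10 | 8 : 2 | 80% |
| 12 | 8 : 4 | 67% |
| 14 | 8 : 6 | 57% |
| 16 or more | equal | 50% |

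**3. Do the totals fit this?** Per class there were 318/21 = 15.1 patients: 187/21 = 8.9 intervention and 131/21 = 6.2 control. The floor alone accounts for 21 × 8 = 168 intervention patients, which leaves 187 − 168 = 19 above it. Under the rule in step 2, those 19 can come only from pools above 16. The excess of 187 − 131 = 56 in the intervention arm can come only from pools below 16, because each contributes 8 − (p − 8) = 16 − p. Under that rule both kinds of pool must have occurred, and the share must have varied. The rule itself is an inference, since the article does not print it.

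**4. Size of a bias.** Assumptions, none given in the article: half the patients come from low-share and half from high-share pools, averaging 59%; the two kinds of pool differ by 0.25 to 0.5 SD after baseline adjustment. With SD 11.8 (Power calculation) that is 2.95 to 5.9 points.

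- Shares 50%/68%: high-share pools make up 0.5 × 0.68/0.59 = 0.576 of the intervention arm and 0.5 × 0.32/0.41 = 0.390 of the control arm. The difference is 0.186. Bias = 0.186 × 2.95 to 0.186 × 5.9 = 0.55 to 1.10 points, or 14% to 27% of the 4.0-point target.
- Shares 55%/63%: 0.5 × 0.63/0.59 = 0.534 and 0.5 × 0.37/0.41 = 0.451. The difference is 0.083. Bias = 0.24 to 0.49 points, or 6% to 12% of the target.

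**5. Simulation.** No treatment effect; 21 pools of one class each; 187 versus 131; 8 to 14 intervention patients per pool; control numbers spread unevenly, with at least 2 per pool; SD 11.8; 1,500 runs per setting; one-sided test at 0.05. Assumed: a pool intraclass correlation of 0.01 to 0.10, and a correlation between pool mean and allocation share as shown. The analysis without pools compares raw means, without baseline adjustment.

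| Correlation with share | Bias without pool term (points) | Type I error without pool term |
|---|---|---|
| 0 | within 0.09 of zero | 0.04 to 0.06 |
| 0.5 | 0.36 to 1.03 | 0.09 to 0.19 |
| 1 | 0.63 to 2.05 | 0.13 to 0.44 |

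With pool effects fitted, bias stays within 0.08 points and type I error is 0.04 to 0.06 in every setting.

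**The case against.** The strongest objection is that this argues from brevity. The Analysis section names no model, and its adjustment set is not declared closed. The Covariates section lists measured patient variables, among which design identifiers would not normally appear. A fuller plan may include hospital or cycle. This stands as a limit on severity. It does not remove the point, because the article does state what it adjusts for, and naming the pool is a concrete change to that statement.

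Second, no allocation ratio per pool is printed. Randomisation waited for a sufficiently large group, so very small pools may never have occurred. Pools of 13 to 15 would give 8/13 = 62% to 8/15 = 53%, narrower than the wider split assumed above. A constant 58.8% in every pool is arithmetically possible if each class drew on about 8/0.588 = 13.6 patients or more, which a mean of 15.1 allows. It fits poorly with a higher chance that is presented as the result of the floor and averaged over recruitment. Variation is the natural reading, but its extent is unknown.

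Third, a reader might infer more than the text supports:

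- *That small hospitals are over-represented in the intervention arm.* A slow recruiter could run fewer classes with pools of the usual size. The article does not link hospital size to allocation share.
- *That differences between class leaders confound the comparison.* Leaders deliver the programme, so their quality changes the treatment effect.
- *That omitting the pool by itself invalidates the test.* With no correlation between pool outcome and share, the simulated type I error is essentially nominal.
- *That the analysis is known to be biased.* Nothing in the article shows that pool outcome and allocation share are related.

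**Conclusion.** The point holds as an improvement, with moderate confidence. Randomisation took place within hospital and cycle under a floor of eight to intervention and against a 1:1 plan, so the allocation share probably varied between pools. The stated adjustment names neither hospital nor cycle. The possible bias is about 0.2 to 1.1 GSES points against the 4.0-point target. That range rests on three assumptions: the share splits, a residual pool difference of 0.25 to 0.5 SD, and that difference lying wholly between high-share and low-share pools. Without such a relation the bias is about zero. The larger simulated figures omit baseline adjustment, which would remove part of them. The article contains no false figure or contradiction on this point, and calling it a must-fix error would go beyond what it shows.

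**What to change.** Include the randomisation pool (hospital by cycle) as a fixed effect, together with the baseline score, in every effect analysis. There are 21 classes and each pool holds at least one, so there are at most 21 levels. If drop-out leaves pools too sparse, use hospital and cycle as separate effects (5 + 10 = 15 degrees of freedom). Report the number per arm in each pool, so that readers can see how far the share varied.

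The cost is a change of wording and at most 20 degrees of freedom among 318 patients. No new data are needed, and follow-up was still being collected when the article was written. Precision is little affected. Under the 50%/68% split the within-pool information is 0.5 × (0.50 × 0.50 + 0.68 × 0.32) = 0.2338 per patient, against 0.59 × 0.41 = 0.2419 without the term. The standard error rises by √(0.2419/0.2338) − 1 = 1.7%, before any gain from removing variation between pools.

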### Intervention

The CDSMP consists of six weekly sessions (two and a half hours per session) and emphasises patients' central role and responsibility in managing their illness [16]. The programme aims to teach patients three types of self-management techniques: dealing with the medical management of the disease (medical management); maintaining, changing, and creating new meaningful behaviours or life roles (role management), and dealing with the emotional consequences of having a chronic condition (emotional management) [18]. These self-management techniques are taught by means of skills mastery through weekly action planning and feedback on progress, modelling of self-management behaviours and problem-solving strategies, reinterpretation of physiological symptoms, and social persuasion through group support and guidance for individual self-management efforts [16,18]. Table 1 shows the CDSMP activities per session. While developing the CDSMP, Lorig and colleagues published the book *Living a healthy life with chronic conditions *[14], as a reference source for the material covered in the sessions. The patients received this book at the first session of the programme. Before the start of the study, the original programme had been translated into Dutch, including *Living a healthy life with chronic conditions *[14]. Some minor adjustments were made in this translated version of the reference book, based on differences between the American and Dutch settings (e.g. with regard to advance directives).

In the original version of the programme, CDSMP classes are led by two trained lay leaders. For the present study, however, we opted for a combination of a 'professional leader' (a CHF nurse specialist) and a 'peer leader' (CHF patient), acting as a role model for the other CHF patients in the class. The reason was that we expect a programme which is led by at least one professional leader to be easier to implement in regular health care than a programme led by two lay leaders only. Furthermore, CHF is a serious disease with unexpected exacerbations and intercurrent health problems. This means that peer leaders may only be able to conduct the programme for a limited period, which could form a threat to the continuity of the programme.

In four of the six hospitals, CHF nurse specialists and CHF patients were trained as leaders. These leaders also conducted CDSMP classes in the two other participating hospitals. A total of twelve professionals and eleven CHF patients received four days of training with the CDSMP protocol in the period April 2004 – November 2005. Four of the twelve professional leaders and two of the eleven peer leaders did not implement the programme in the intervention period, due to work, health, or private issues. Each of the groups in which the leaders were trained (n = 4 to 6) included both professional leaders and peer leaders, who practised together, to provide an optimal training situation. The leader training was provided by one of the researchers ([name]) and a CHF nurse specialist of the University Hospital Maastricht in the Netherlands. Both had been instructed as master trainers at Stanford University by Lorig and colleagues in March 2004. The nurse master trainer also conducted several classes in the intervention period.

